### Design and interventions

In this study, we conduct a two-arm randomized controlled trial among GPs. GPs in both study arms receive personalized electronic FBRs every two months during a consecutive study period of 12 months, each containing information pertaining to an assessment period of 12 months prior to the respective time of FBR delivery. On the days of FBR delivery, participating GPs receive an email containing a password-protected link to their personalized electronic FBR as portable document format (PDF) documents, which can be viewed in an internet browser or downloaded.

The regular provision of personalized electronic FBRs with descriptive summaries of patient demography and events of care has already been established as a standard in the FIRE database. These plain FBRs (P-FBRs) do not contain any QI-specific information, but are intended as a tool for the GPs to monitor their practice activities over time, and thus as an incentive to participate in the FIRE project. GPs in the control arm of this study receive such P-FBRs containing information on the number of treated patients, demographic summaries, and descriptive summaries of the frequencies and results of selected laboratory tests, blood pressure readings, chronic conditions, and drug prescriptions occurring during the respective assessment period. Participants of the FIRE project did not receive any P-FBRs during the years 2022–2023, since usability of the FIRE database was limited due to updates and technical innovations during this time. Therefore, neither the GPs already enrolled in the FIRE project nor newly enrolled GPs had any recent exposure to electronic FBRs at study start.

GPs in the intervention arm receive comprehensive individualized FBRs (QI-FBRs) including information concerning the 14 QIs selected as described in the previous section. For the respective assessment period, each QI-FBR includes all 14 PS_QI_s of the recipient, the changes of the PS_QI_s with respect to the previous assessment period, and the distribution of the PS_QI_s across all GPs in the FIRE database.

Both the P-FBR and the QI-FBR are two-page PDF documents presenting information with a mix of infographics and tables. Examples of a P-FBR and of a QI-FBR are shown in S3 and S4 Appendices, respectively.

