### Participants and ethics

The participants were recruited among GPs formally enrolled in the FIRE project who have been contributing data to the FIRE database. For GPs enrolled in the FIRE project before December 31, 2023, we defined the study start at January 01, 2024. For GPs joining the FIRE project at later times, we defined individual study starts as the earliest date among March 01 or May 01, 2024, following enrolment in the FIRE project. All eligible GPs were notified of the study via email with an information sheet and were enrolled automatically, with the option to decline participation before randomization (opt-out approach).

To be eligible, GPs had to have worked in their respective practices for at least one year prior to their respective start of the study and be board certified as GPs (either in general internal medicine or in general medical practice). GPs were excluded if they did not use the designated entry field in their electronic medical records to record necessary data, such as diagnoses and laboratory values, or if they were already enrolled in different audit and feedback processes involving the FIRE project. The study flow chart is presented in Fig 3.

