### Statistical analysis

We will provide tabular summaries of the demographic and professional characteristics of included GPs at baseline, including distributions of QI performance.

We will analyze the primary study outcome using an intention-to-treat (ITT) framework, considering each GP according to the study arm to which they are randomized, regardless of whether they may have requested to receive the respective other FBR at some point during the study period. For each GP, we call the 12 months preceding their individual study start the baseline period and the 12 months from study start to study end the follow-up period, respectively. We will use a binomial regression model in a dataset that includes, for each GP in the ITT population, one observation each for the baseline and follow-up periods. The total number of events and of successes will be given by the sizes of the corresponding denominator and numerator populations, respectively, for the corresponding GP, QI, and assessment period. We will use a mixed-effects model to account for each GP contributing two observations to the dataset (normally distributed GP-level random intercepts) and to account for unobserved effects on the practice level (normally distributed practice-level random intercepts) [26]. The model will include an indicator for the baseline versus the follow-up period, to assess the general effect of FBRs on QI performance, and an indicator for the QI-FBR arm versus the P-FBR arm during the follow-up period, to assess the differential effect of the QI-FBR in addition to the P-FBR on QI performance. In addition, we will adjust for the covariates used for balanced allocation (GP sex and workload). We will assess the primary study outcome by considering the statistical significance at the 0.05 level of the coefficient estimate associated with the indicator for the QI-FBR arm versus the P-FBR arm during the follow-up period.

GPs leaving the FIRE project, GPs whose practice eventually fails to export all relevant data to the FIRE database, and GPs who wish to opt out from the study during the study period after randomization will be considered as drop-outs.

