### Power and sample size

Since we aimed to enroll as many GPs as possible among the GPs contributing to the FIRE project, we did not define a specific sample size to be achieved. Instead, we conducted a power analysis using model-based simulations to determine the statistical power resulting from different GP sample sizes and from different assumptions about the general effect of an FBR (any of the QI-FBR or P-FBR versus no FBR) on QI performance [27]. We based this power analysis on the intended final analysis described in the statistical analysis section and used estimates from a sample of 64 GPs enrolled in the FIRE project through 31 December 2023 who satisfied the eligibility criteria (details of the simulation in S6 Appendix). The overall QI performance across all GPs observed in this sample was 35.6%. We considered the following hypothetical levels of general FBR effects: OR of 1.0 (no effect), 1.3 (corresponding to the lower end of the FBR effects observed in the previously mentioned trial in the FIRE project involving diabetes care [21]), and 2.0 (corresponding to the upper end of the effects observed in this previous trial). For the differential effect of the QI-FBR versus the P-FBR, we assumed an absolute increase of 2 percentage points in the overall QI performance (corresponding to an OR of 1.09 in the observed sample), which is a small effect size compared to the 10 percentage point improvement often assumed in power analyses of previous studies involving performance feedback on similar QIs [28–31]. Relevant GP characteristics, including the adjustment covariates planned for the final analysis and the size of the denominator populations, were accounted for by bootstrapping from the observed sample of 64 GPs. With this constellation, assuming 1:1 allocation and with an alpha of 0.05, power was determined to be at least 88% with a total sample size of at least 50 GPs, regardless of assumptions about general FBR effects. Assuming a drop-out rate of 10%, which is slightly higher than that observed in the aforementioned previous trial within the FIRE project [20], a sample size of 56 GPs would ensure a statistical power of 88% to detect a 2 percentage point increase in overall QI performance across all GPs. We performed this power analysis using the statistical software R version 4.3.2 (R Foundation for Statistical Computing, Vienna, Austria) and used the lme4 package for mixed-effects modelling [32,33].

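### The baseline-versus-follow-up coefficient is described as the general effect of feedback reports, but with reports in both arms it is only the uncontrolled before-after change in the P-FBR arm

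*Protocol article*

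**What the plan says.** The Statistical analysis section specifies a binomial mixed model with one baseline and one follow-up observation per GP. It contains two indicators of interest. The first is "an indicator for the baseline versus the follow-up period, to assess the general effect of FBRs on QI performance". The second marks the QI-FBR arm during follow-up, and the primary test at the 0.05 level uses only that second coefficient.

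The Power and sample size section spells out what the first indicator is meant to capture: the "general effect of an FBR (any of the QI-FBR or P-FBR versus no FBR". It considers hypothetical odds ratios of 1.0, 1.3 and 2.0 for it.

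The Design and interventions section states that "GPs in both study arms receive personalized electronic FBRs every two months during a consecutive study period of 12 months". It adds that no P-FBRs were sent in 2022–2023 because "usability of the FIRE database was limited due to updates and technical innovations during this time".

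On timing, "we call the 12 months preceding their individual study start the baseline period". Study start is 1 January 2024 for GPs already enrolled in FIRE, and 1 March or 1 May 2024 for those who joined later (Participants and ethics).

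**The concern.** The protocol assigns a causal meaning, report versus no report, to a coefficient that rests on no randomised or concurrent comparison. The only time without reports is each GP's own preceding year. Whatever else changed between the two years goes into the same coefficient: secular trend in care, differences between two particular years (including the influenza vaccination seasons behind two of the indicators), and any change in how data are recorded or captured.

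A period coefficient different from zero would, on the plan's stated reading, be reported as an effect of feedback. The Limitations section does not qualify this. An SAP is not being asked to fill a gap here: the protocol states an interpretation that its design does not support.

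**Working it through.** **1. What the coefficient estimates.** Leaving covariates aside, the model for GP *i* in period *t* is

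logit P = a_i + β·(follow-up) + δ·(follow-up × QI-FBR arm).

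- P-FBR arm: follow-up minus baseline = β.
- QI-FBR arm: follow-up minus baseline = β + δ.

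So β is in essence the P-FBR arm's before-after change. If *r* is the log odds ratio of the plain report against none and *d* is a drift common to both arms, then β = r + d. Nothing in the data separates r from d. The drift cancels from δ.

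**2. Where the baseline year lies.**
- Round 1: January to December 2023, so 12 of 12 months fall in 2022–2023.
- Round 2: March 2023 to February 2024, so 10 of 12.
- Round 3: May 2023 to April 2024, so 8 of 12.

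Most baseline time therefore falls in the years of the database updates. Each baseline and each follow-up window contains exactly one October–December season, so the vaccination indicators compare one season with the next.

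**3. The plan's own figures.** (0.376/0.624)/(0.356/0.644) = 1.090, matching the stated odds ratio of 1.09. 50/0.9 = 55.6, rounded up to 56, also matches. The 88% power comes from a simulation with GP denominators given in S6 Appendix, which is not shown, so it cannot be reproduced. A within-GP approximation with 25 GPs per arm and equal denominators *m* per GP and period, SE(δ) = √(4/(25·m·0.356·0.644)), gives power of 78%, 87% and 90% for m = 700, 900 and 1000. That is the only basis for using about 900 below.

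**4. Period odds ratio produced by drift alone (r = 0), from 35.6%.**

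| Drift (percentage points) | Period OR |
|---|---|
| 1 | 1.04 |
| 2 | 1.09 |
| 3 | 1.14 |
| 5 | 1.24 |

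**5. Drift needed for nominal significance.** With 25 P-FBR GPs, SE(β) = √(2/(25·m·0.356·0.644)), and the threshold in percentage points is 100 × 1.96 × SE × 0.356 × 0.644. Alpha is taken as two-sided; the protocol does not state this.

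| Assumed m | SE(β) | Threshold (percentage points) |
|---|---|---|
| 300 | 0.034 | 1.5 |
| 500 | 0.026 | 1.2 |
| 700 | 0.022 | 1.0 |
| 900 | 0.020 | 0.9 |
| 1500 | 0.015 | 0.7 |

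**6. Simulation.** Settings: 50 GPs, m = 900, between-GP SD 0.5 on the logit scale (both assumed), GP effects fitted as fixed, no practice level, arm effect OR 1.09, 200 runs per scenario.

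| Drift OR | True report OR | Period OR | Period term p<0.05 | Arm OR |
|---|---|---|---|---|
| 1.00 | 1.00 | 1.00 | 4.5% | 1.09 |
| 1.045 | 1.00 | 1.04 | 59.5% | 1.09 |
| 1.09 | 1.00 | 1.09 | 99% | 1.09 |
| 1.30 | 1.00 | 1.30 | 100% | 1.09 |
| 1.00 | 1.30 | 1.30 | 100% | 1.09 |
| 1.19 | 1.09 | 1.30 | 100% | 1.09 |

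The last three rows are indistinguishable in the period term, although the true report effect ranges from none to 1.30. The arm odds ratio stays at about 1.09 throughout.

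**The case against.** The strongest reply is that nothing depends on this coefficient. The Objectives section concerns only QI-FBR versus P-FBR, the primary test uses only the arm coefficient, the secondary analyses all concern the QI-FBR, and no test or conclusion is announced for the period term. The term has to be in the model anyway. All of this stands, and it limits the point to interpretation. It does not rescue the stated purpose, which the protocol gives in one section and defines as report versus no report in another.

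Several stronger readings are tempting and should not be made:

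- *Baseline data were deficient.* A reader might infer this from the database updates. The protocol gives limited usability only as the reason why no reports were sent. It does not say that baseline QI data were incomplete, and it excludes GPs who do not use the designated entry fields. A change in data capture is plausible but not documented. The comparison is uncontrolled whatever the state of the database.
- *The primary result is biased.* Common drift cancels from the randomised contrast, as the working shows.
- *The plan assumes a general effect of OR 1.3.* That is one of three hypothetical scenarios, and the stated power holds under all of them.
- *The result will be published or sent to the Federal Quality Commission as an effect of feedback.* The Dissemination plans section does not say that this contrast will be reported.

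One could also look to the later start dates for a concurrent comparison without reports. Those GPs are newly enrolled, start only two or four months later, and enter the model through the same single period indicator, so they supply no usable control.

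**Conclusion.** The point holds as a matter of interpretation. The design does not identify the effect of a report versus no report, and the period coefficient should not be described as assessing it. This follows from the model and from both arms receiving reports; it needs no assumption about the size or cause of any drift.

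The size is illustrative. At an assumed 900 denominator records per GP and period, a drift of about 1 percentage point suffices for nominal significance (0.7 to 1.5 points for 1500 down to 300 records). Equal denominators are assumed, whereas the protocol's simulation resampled observed GPs. The randomised comparison, its alpha and its power are unchanged. The wording should be corrected because it governs what the trial may conclude about feedback in general.

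**What to change.** Keep the period indicator in the model. Replace its stated purpose with wording such as: *to account for the before-after change in the P-FBR arm, which the design cannot attribute to feedback*. Use the same description for the corresponding scenarios in the Power and sample size section. Confine all statements of effect to the randomised QI-FBR versus P-FBR contrast.

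Do not add a comparison with non-participating FIRE GPs by default, although the earlier FIRE trial drew on one (Setting and data source). Enrolment here was opt-out, so non-participants are mainly decliners or ineligible GPs, and P-FBRs are standard in FIRE, so they may have received reports too. Only if a group that demonstrably received no reports exists should such a comparison be made, and it should then be labelled non-randomised.

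The cost is wording only: no change to the model, data, sample size or primary test.

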### Power and sample size

Since we aimed to enroll as many GPs as possible among the GPs contributing to the FIRE project, we did not define a specific sample size to be achieved. Instead, we conducted a power analysis using model-based simulations to determine the statistical power resulting from different GP sample sizes and from different assumptions about the general effect of an FBR (any of the QI-FBR or P-FBR versus no FBR) on QI performance [27]. We based this power analysis on the intended final analysis described in the statistical analysis section and used estimates from a sample of 64 GPs enrolled in the FIRE project through 31 December 2023 who satisfied the eligibility criteria (details of the simulation in S6 Appendix). The overall QI performance across all GPs observed in this sample was 35.6%. We considered the following hypothetical levels of general FBR effects: OR of 1.0 (no effect), 1.3 (corresponding to the lower end of the FBR effects observed in the previously mentioned trial in the FIRE project involving diabetes care [21]), and 2.0 (corresponding to the upper end of the effects observed in this previous trial). For the differential effect of the QI-FBR versus the P-FBR, we assumed an absolute increase of 2 percentage points in the overall QI performance (corresponding to an OR of 1.09 in the observed sample), which is a small effect size compared to the 10 percentage point improvement often assumed in power analyses of previous studies involving performance feedback on similar QIs [28–31]. Relevant GP characteristics, including the adjustment covariates planned for the final analysis and the size of the denominator populations, were accounted for by bootstrapping from the observed sample of 64 GPs. With this constellation, assuming 1:1 allocation and with an alpha of 0.05, power was determined to be at least 88% with a total sample size of at least 50 GPs, regardless of assumptions about general FBR effects. Assuming a drop-out rate of 10%, which is slightly higher than that observed in the aforementioned previous trial within the FIRE project [20], a sample size of 56 GPs would ensure a statistical power of 88% to detect a 2 percentage point increase in overall QI performance across all GPs. We performed this power analysis using the statistical software R version 4.3.2 (R Foundation for Statistical Computing, Vienna, Austria) and used the lme4 package for mixed-effects modelling [32,33].

### Secondary analyses

We will conduct secondary analyses to examine the effect of the QI-FBR by chronic condition domain and by individual QI. In addition, we will examine the variation of the effect of the QI-FBR with different download frequencies. All secondary analyses will involve the regression model described in the statistical analysis section extended by appropriate interaction terms. We will address the global hypotheses of whether the QI-FBR is effective on performance in any of the chronic condition domains or in any of the QIs by considering the *p*-values associated with the inclusion of the respective interaction terms.

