### Quality indicator selection

The selection process for the QIs included in the study involved a comprehensive and iterative multi-step approach. Its aim was to identify a set of relevant and practicable QIs reflecting the above-mentioned specialty domains of medical practice.

To start, we thoroughly reviewed the existing literature, clinical guidelines, and best practices related to chronic conditions in the specified specialty domains of medical practice. The purpose was to identify potential QIs that had previously been validated or recommended in the literature and guidelines and that may be assessed in the FIRE database.

Following the literature review, we consulted a leading medical expert for each of the four specialty domains to gain insight and recommendations on the relevance and the potential impact of the QIs belonging to the respective domain.

In a next step, we engaged in discussions with a panel of six GPs practicing in different regions of German-speaking Switzerland who had extensive practical experience in providing care for the chronic conditions from all specified specialty domains. These GPs served as representatives from the study population and helped to gather perspectives and feedback on the perceived relevance, practicability and potential impact of the identified QIs. These discussions helped ensure applicability and acceptance of the selected QIs.

Based on the information gathered from the literature review, expert consultations, and panel discussion, the study team decided on the selection and definition of the QIs to be included in the FBRs, aiming to balance scientific rigor, relevance, and acceptance. The QI selection process is summarized in Fig 2. The final definitions of the 14 selected QIs (5 in the cardiovascular, 3 in the endocrine, 3 in the pulmonary, 3 in the renal domain) are presented in Table 1. The operationalized criteria for the corresponding conditions mentioned in the definitions of the denominator populations and for QI achievement are presented in S2 Appendix.

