### Objectives

The primary study objective is to compare the effectiveness of the QI-FBR and of the P-FBR with respect to the overall QI performance. As secondary study objectives, we will compare the effectiveness of the QI-FBR and of the P-FBR with respect to QI performance in the different specialty domains considered.

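### The test planned for whether the QI-FBR works in any domain or any QI is, as written, a test of whether its effect differs between them

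*Protocol article*

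**What the plan says.** All places are in the protocol article.

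- **Objectives.** The secondary aim is stated as "we will compare the effectiveness of the QI-FBR and of the P-FBR with respect to QI performance in the different specialty domains considered". It is the only secondary objective, and under Outcomes the changes in the domain scores are the only secondary outcomes.
- **Statistical analysis.** The primary model has a period indicator and "an indicator for the QI-FBR arm versus the P-FBR arm during the follow-up period, to assess the differential effect of the QI-FBR". This is one common effect of the QI-FBR.
- **Secondary analyses.** "All secondary analyses will involve the regression model described in the statistical analysis section extended by appropriate interaction terms". The section goes on: "We will address the global hypotheses of whether the QI-FBR is effective on performance in any of the chronic condition domains", or in any QI, and the answer is to come from the p-values "associated with the inclusion of the respective interaction terms".
- **Quality indicator selection.** There are 14 QIs in four domains: "5 in the cardiovascular, 3 in the endocrine, 3 in the pulmonary, 3 in the renal domain".

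The Secondary analyses section also says that the effect will be examined by domain and by QI. For the global hypotheses it names no joint test against zero and no rule about the direction of effect.

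**The concern.** The hypothesis and the test have different nulls. The hypothesis of no effectiveness in any domain says that every domain-specific effect is zero. Adding interaction terms to a model that keeps a common effect tests only whether the domain-specific effects are equal to one another. They can be equal and large.

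At stake is the answer to the only secondary objective. A report that helps equally in all domains gives null interactions, so the planned p-value would usually be read as no effectiveness in any domain, possibly beside a significant primary result. A uniform benefit is not far-fetched: the power analysis, as the article describes it, assumes a single overall effect and mentions no domain-specific ones.

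**Working it through.** **Inputs.** From Power and sample size: observed performance 35.6%; assumed gain of 2 percentage points, stated as OR 1.09; alpha 0.05 (taken as two-sided, which the article does not say); power of at least 88% with at least 50 GPs; drop-out 10%; 56 GPs. From Quality indicator selection: K = 4 domains, K = 14 QIs.

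**1. The plan's own figures.** OR = (0.376/0.624) / (0.356/0.644) = 0.6026/0.5528 = 1.09. Sample size: 50/0.90 = 55.6, rounded up to 56. Both reproduce. The 88% comes from simulation, and the denominators and variance components behind it are not in the article, so it is taken as stated.

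**2. The two nulls.** Let δ_k be the log odds ratio of QI-FBR versus P-FBR at follow-up in domain (or QI) k.

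- The primary model has a single δ. Extending it gives δ_k = δ + γ_k with K − 1 free γ's. The p-value for including them tests γ = 0, that is δ_1 = … = δ_K, with δ left free: 3 df for domains, 13 df for QIs.
- The stated hypothesis has the null δ_1 = … = δ_K = 0: 4 df for domains, 14 df for QIs.

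**3. Uniform benefit under the planned test.** If all δ_k are equal, every γ_k is zero and the noncentrality is 0. The test rejects in 5% of trials and misses the benefit in 95%. This is the same for a uniform OR of 1.09, 1.19 or 1.30.

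**4. Uniform benefit under a joint test.** A power of 88% in a two-sided 1-df test implies a noncentrality of (1.960 + 1.175)² = 3.135² = 9.83. The working assumes equal information per domain or QI, although for a uniform effect the split does not change the joint test's noncentrality. Power is the upper tail of the noncentral chi-square beyond its 5% critical value:

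| Uniform OR 1.09 | Planned interaction test | Joint test of all effects = 0 |
|---|---|---|
| Domains | 5.0% (3 df) | 70.7% (4 df) |
| QIs | 5.0% (13 df) | 46.5% (14 df) |

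**5. Simulation check, domains only.** Logistic model, 50 GPs, 4 domains, 2 periods, 500 replicates, with an assumed 270 patients per cell. Under a uniform OR of 1.09 the rejection rates were 91.4% for the primary 1-df test, 5.8% for the interaction test and 79.0% for the joint test. With no effect anywhere they were 5.0%, 5.0% and 4.6%.

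**6. The other direction.** Suppose harm in one domain (OR 1/1.09² = 1/1.19) and no effect in the other three. With β = log 1.09 and equal information per domain, the mean effect is −0.5β.

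- Interaction noncentrality: 9.83 × (3 × 0.5² + 1.5²)/4 = 9.83 × 0.75 = 7.37, so it rejects in 61%.
- Joint noncentrality: 9.83 × 2²/4 = 9.83, so it rejects in 71%.
- With information split 5/3/3/3 and the harm in a domain of three QIs: 56% and 63%.
- In the simulation: 96% and 97%.

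In each version the joint test rejects at least as often as the interaction test although no domain benefits. The spread from 56% to 96% shows how far these rates depend on assumed information.

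**The case against.** **The reading.** The article gives no degrees of freedom and no reference model. The primary QI-FBR term is itself an arm-by-period product with no arm main effect listed, so domain-specific QI-FBR follow-up terms could also be called interaction terms. Testing all of them against no QI-FBR term would be the right test. The fuller protocol may say so. This reading is possible, but it conflicts with the statement that the described model is extended, since that model already holds the common term. Nor is this a matter of missing detail: the article names a hypothesis and names the p-value that is to answer it.

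**The consequence.** A uniform benefit is what the primary test is powered to detect, and effects by domain and by QI are to be examined anyway. Readers with a significant primary result and similar domain effects might not be misled by one omnibus p-value. This stands and limits the damage. It does not make the p-value answer the stated question.

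**A stronger reading.** A reader might infer that the planned test fails equally in both directions and that a joint test cures both. The documents do not support that. If the report helps one domain and harms another, effectiveness in some domain is true and a significant result is right. Uniform harm, like no effect at all, leaves the interaction test at 5%. A significant result misleads only when effects differ between domains and none is beneficial, and an unsigned joint test has the same weakness there.

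**Conclusion.** The concern holds for the loss of a uniform benefit. The 95% miss rate follows from the wording alone: it needs equal odds ratios across domains or QIs and a reference model that keeps the common QI-FBR effect, but no assumed sample size, variance or effect size.

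The power figures for the joint test are illustrative. They treat a power of at least 88% as exactly 88%, take the test as two-sided, and carry the primary model's information into a domain- or QI-level model whose variance structure is not given. The false-positive direction is narrow and is a matter of sign, not of which omnibus test is used.

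The primary objective, outcome, test and sample size are untouched. The point deserves correction before the unblinded analysis because it bears on the only secondary objective, but it does not threaten the trial's main conclusion.

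**What to change.** In Secondary analyses:

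1. Test each global hypothesis by comparing a model with all domain-specific (or all QI-specific) QI-FBR follow-up effects against an otherwise identical model with no QI-FBR effect, by a likelihood-ratio or joint Wald test on 4 df (or 14 df).
2. Report the domain- and QI-specific odds ratios with their sign and 95% confidence intervals, and claim effectiveness only where the effect is a benefit. This step, not the joint test, deals with harmful effects.
3. Keep the 3-df and 13-df interaction p-values, labelled as tests of heterogeneity.

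If the joint test was intended all along, a sentence naming the reference model is enough. Adjusting the domain-specific p-values for multiplicity is optional and not part of this point.

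The cost is a small text change and one extra reduced model for each global hypothesis, or none if a joint Wald test is used. No new data are needed and the sample size does not change.
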